#### **4.2 Duration of study participation**

The total duration of participation in the study for a patient is 48 hours.

#### **4.3 Timetable of the study**

- Submission to the ICC Technical Committee of Clermont-Ferrand: 30/11/2009
- Submission to the South East CPP VI (Ethics Committee): January 2010
- Submission to the AFSSAPS: January 2010
- Start of inclusions: favorable opinion from the CCP
- Length of Inclusions: 1 year
- Statistical Report: March 30, 2011
- Final Report: June 31, 2011

### **5 Population studied**

#### **5.1 Inclusion criteria**

- Age ≥ 18 years
- Duration of mechanical ventilation > 48 hours
- Indwelling arterial catheter
- Patient considered stable under PSV
  - pressure support ≤ 8 cmH2O - PEEP ≤ 5 cmH2O - FiO2 ≤ 40% - SpO2 ≥ 95% - Respiratory Rate (RR) ≤ 20/min, tidal volume (Vt) > 7 ml/kg of ideal body weight
  - Glasgow Coma Scale ≥ 13 and interruption of sedation
  - Body temperature < 38°C
  - No vasopressor support and a systolic blood pressure (SBP) < 160 and > 100 mmHg.
- Informed consent from the patient (or from next of kin if the patient is not able to speak)
- Patient under French Social Security system

#### **5.2 Non-inclusion criteria**

- Refusal of the patient or his designated person of trust
- Tracheotomy
- Trauma with spinal paraplegia above T8 level
- Cardiac arrhythmias (atrial fibrillation) or electrostimulation
- Absence of patient echogenicity at the thoracic level

### **5.3 Criteria for exclusion**

- Respiratory distress due to postextubation laryngeal disease (e.g., airway obstruction, spasm) and requiring reintubation

### **5.4 Period of exclusion**

At the end of patient follow-up in this study, no exclusion period is required.

### **5.5 Methods of recruitment**

The eligibility of patients is sought during the visit and the medical staff who place each morning in the intensive care unit. The final inclusion takes place in the morning for patients meeting the criteria for inclusion and exclusion, with the approval of patient or his designated person of trust.

## **6 Statistical Considerations**

### **6.1 Power calculation**

This study is a pilot study, and data are lacking to establish an expected difference between the two sub-groups on the primary endpoint.

So we justify the feasibility this pilot study by recruitment forecasts and allocation among the sub-groups. Thus, we analyze the data from the observation of 30 patients failing extubation at 48th hour. These patients are in large published series approximately 35% of patients who passed the test of weaning (1-4, 7, 22). SBT failure is found in about 15% of eligible patients in published series (22).

Therefore a total of 100 patients will enable us to study 85 patients passing SBT and thus compare 55 patients without extubation failure with 30 patients failing extubation at 48 hours.

### **6.2 Processing of statistical data:**

Population will be described with regards to demographic and clinical characteristics by percentages or numbers for qualitative and categorical variables, and averages ( $\pm$  standard deviation) or medians (with interquartile ranges) when appropriate.

For primary endpoint analysis, the mean difference before and after SBT will be compared between the patients in the "weaning failure" group and patients in the "successful weaning" group by Student's t test if variables are normally distributed. Normal distribution will be tested by the test Kolmogorov-Smirnov test) and in the case of non-normal distribution, Mann-Whitney (or Wilcoxon) test will be applied. Predictive values of LUS will be determined by ROC (Receiving operating characteristics) curves.

Following tests will applied for secondary endpoints analyses:

- Correlation tests (Pearson / Spearman) for comparisons of changes in LV filling pressure (E/Ea) and BNP levels.
- Comparisons of mean changes in E/Ea and BNP between subgroups (success and failure of weaning).
- Comparisons of mean changes between LUS in patients failing SBT and those in patients passing SBT.

The center-effect will be measured by the coefficient of intra-class correlation and taken into account in the different statistical analyses when necessary.

For all tests, the risk of error is set at  $\alpha$  (alpha)=0.05. For each test we will reject the null hypothesis (hypothesis of no difference) for p-values below 0.05. Data will be entered into an Access database, checked, then analyzed using Stata V10 software ([name]).

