#### 3.2 Evaluation criteria

##### 3.2.1 Primary Outcome

The primary endpoint is the assessment of lung aeration scores Pulmonary (*Lung Ultrasound Score*) test before and after SBT, and after extubation. We will use the lung aeration score proposed and validated by [name] (16). No additional mobilization of the patient is necessary. Each thoracic quadrant is scanned in its entirety by the ultrasound probe, and points are attributed: 0 points = Ventilation normal lung sliding single or "N"; 1 = tails of comets spaced "B1"; 2 = tails comets curtains "B2"; Consolidation 3 = "C". The score is an average score obtained at each phase of weaning. We will also evaluate the variation of aeration in its entirety.

[figure not shown]

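### The primary test is picked by a Kolmogorov-Smirnov normality check that is far off its nominal level in ordinary form and leaves means versus ranks to be settled by the data

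*Protocol*

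**What the plan says.** Protocol section 6.2 compares the before/after SBT change in LUS between the weaning-failure and weaning-success groups "by Student's t test if variables are normally distributed". It then states how this is decided: "Normal distribution will be tested by the test Kolmogorov-Smirnov test) and in the case of non-normal distribution, Mann-Whitney (or Wilcoxon) test will be applied". No correction for estimated parameters is named, and no reference mean or SD is given. The same section sets one threshold throughout: "For each test we will reject the null hypothesis (hypothesis of no difference) for p-values below 0.05".

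Section 6.1 calls the study a pilot and says that "data are lacking to establish an expected difference between the two sub-groups on the primary endpoint". It gives no SD either. The planned groups are stated there: "a total of 100 patients will enable us to study 85 patients passing SBT and thus compare 55 patients without extubation failure with 30 patients".

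Section 3.2.1 builds the score from points 0 to 3 per lung region, averaged at each phase of weaning.

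**The concern.** The ordinary Kolmogorov-Smirnov (K-S) test of normality assumes that the mean and SD are known beforehand. Here neither is given, so both must be estimated from the patients being tested. The fitted curve then follows the sample too closely, and the usual critical value is too large. A check meant to flag non-normal data will rarely do so.

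There is a separate problem that calibration does not touch. The t test compares means, and Mann-Whitney compares the ordering of patients. Under the stated rule the data choose which is the primary hypothesis. When the two tests fall on opposite sides of 0.05, the preliminary check settles the study's primary conclusion.

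**Working it through.** **1. The plan's group sizes.** From 100 enrolled, "SBT failure is found in about 15% of eligible patients in published series (22", so 100 × (1 − 0.15) = 85 pass. Extubation failure is put at "approximately 35% of patients who passed the test of weaning": 85 × 0.35 = 29.75, about 30, and 85 × 0.65 = 55.25, about 55. The plan's figures reproduce and are used below.

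**2. Level of the normality check.** K-S distances were simulated for 20,000 normal samples per size, each standardised by its own mean and SD, and compared with the ordinary 5% critical value.

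| n | Ordinary critical value | Critical value corrected for estimation (Lilliefors) | Ratio | Actual rejection rate |
|---|---|---|---|---|
| 30 | 0.242 | 0.159 | 1.52 | 0.005% (1 of 20,000) |
| 55 | 0.180 | 0.119 | 1.51 | 0.01% (2 of 20,000) |
| 85 | 0.145 | 0.097 | 1.49 | 0.03% (6 of 20,000) |

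The counts are small, so only the order of magnitude matters; a separate 40,000-sample run gave 0.010 to 0.013%. The level fails whether normality is checked per group or pooled, which the protocol does not say.

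**3. Detection of non-normality.** For the share of trials at 30 versus 55 in which the check fires in either group (10,000 runs per shape):

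| Assumed shape | Ordinary K-S | Corrected K-S |
|---|---|---|
| Normal | 0.03% | 9.2% |
| Gamma, shape 4 (skewness 2/√4 = 1) | 3% | 57% |
| Lognormal, sigma 0.5 | 17% | 86% |
| t with 3 df | 17% | 68% |
| Exponential | 52% | 99% |
| Lognormal, sigma 1 | 93% | 100% |

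In a single group with gamma data of skewness 1.4, ordinary K-S missed the skew in 97 to 98% of samples at n = 30 and 90 to 91% at n = 55. Shapiro-Wilk missed 25 to 26% and 3%.

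**4. Type I error of the whole rule.** With the same distribution in both groups, the rule (K-S in each group, Mann-Whitney if either rejects, otherwise Student's t) rejected in 4.5 to 6.1% of null trials across the shapes tried. The highest figure was for exponential data, where the t test alone gave 5.3% and Mann-Whitney alone 5.1%.

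**5. How often the choice matters.** The two tests gave different decisions at 0.05 in 1.7 to 5.1% of null trials. Under an assumed shift of 0.64 SD they differed in about 5 to 18%.

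**6. Power under an assumed 0.64 SD shift** (30 versus 55, 2,000 runs):

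| Assumed shape | Gated rule | Mann-Whitney | Difference | Permutation test of means |
|---|---|---|---|---|
| Normal | 79% | 77% | −2 | 78% |
| Gamma, skewness 1.4 | 81% | 91% | 10 | 80% |
| Lognormal, sigma 0.5 | 84% | 93% | 9 | 81% |
| t with 3 df | 89% | 96% | 7 | 84% |
| Exponential | 90% | 97% | 7 | 81% |
| Lognormal, sigma 1 | 99.8% | 100% | 0.2 | 86% |

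The loss against a rank test is 7 to 10 points for the four middle shapes. It vanishes for extreme skew, because the check then fires nearly every time.

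**7. Unequal spread.** With normal data, equal means and twice the SD in the smaller failure group, the gated rule rejected in 10.5%, Student's t in 10.5%, Mann-Whitney in 8.0% and Welch in 5.1%. The excess comes from the pooled-variance t test, since the gate did not change the figure. It does bear on the choice of replacement.

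**The case against.** The best defence is that little follows from the defect. A check that seldom fires simply defaults to the t test, which holds its level well at 30 and 55 patients. A reader might infer that the gate inflates false positives. The simulations do not support that: with like distributions in both groups the error stays at about 4 to 6%. This part of the defence stands.

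Secondly, the protocol does not exclude a Lilliefors correction, and the 5% level for the normality check is inferred from the blanket threshold, whose wording concerns a null of no difference. This stands as a limit on the calibration argument. It leaves the data-driven choice of hypothesis untouched.

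Thirdly, because the score is built from whole points, a reader might infer that ties drive the gate. Rounding normal data to integers sent 94% of trials to the rank test at an SD of 1 point, 9% at 2 and 1% at 3. The result thus depends on the coarseness assumed. Section 3.2.1 says that the score is averaged, and its readable text does not fix how many regions enter or how much tying results. No figure for this trial can be drawn.

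Fourthly, a reader might infer that any fixed test would recover the lost power. It would not: the last column of the power table shows a mean-based test level with or below the gated rule for the skewed and heavy-tailed shapes.

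Finally, this is a pilot sized on feasibility with no power target, so the power differences contradict no planned figure.

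**Conclusion.** The point holds in a limited form and should be corrected. The rule is written into the protocol, so this is not a detail merely left for later. As named, the check does not work as a 5% test of normality, and with or without a correction it leaves the primary hypothesis open until the data are seen.

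The cost is a primary p-value that depends on an unreliable preliminary test in the roughly 5 to 18% of trials where the two tests disagree, and 7 to 10 points of power against a rank test for several skewed or heavy-tailed shapes. It is not a material inflation of type I error.

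These sizes assume ordinary K-S with estimated parameters, two-sided tests, groups of 30 and 55, a pure shift of 0.64 SD and the listed shapes. The protocol gives no SD, effect or distribution for LUS change, so the power and disagreement figures are illustrations. Only the failure of the level is free of assumptions about effect or shape, and it presumes no correction.

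**What to change.** Delete the normality check from section 6.2 and name one primary test of LUS change. One option is Mann-Whitney with a Hodges-Lehmann estimate and 95% CI, with the mean difference and its Welch 95% CI as a fixed sensitivity analysis. If the mean difference is the intended quantity, reverse the two and accept lower power under skew. Apply the same rule to the E/Ea and BNP changes.

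The team should make the choice knowingly. If spread is expected to be larger in the failure group, Welch kept its level in the unequal-spread check (5.1%) and Mann-Whitney did not (8.0%). In either order, Welch should replace Student's t.

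The cost is a sentence or two of protocol wording, and about 2 to 3 points of power if a rank test is chosen and the data turn out exactly normal.

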### ***13 Communication - Publishing Rules***

### ***14 List of appendices***

### ***15 Bibliography***

## **1 Rationale of the study:**

Weaning from mechanical ventilation is a critical period in intensive care unit (ICU) patients (1, 2). Weaning failure includes initial spontaneous breathing trial (SBT) failure, postextubation distress and death occurring within 48h following extubation (1). Postextubation distress is defined as reintubation or need for non-invasive ventilation within 48 hours following extubation (1, 3). Following a successful SBT, incidence of reintubation ranges between 3 and 30% (1, 3). Postextubation distress after a successful SBT is associated with increased morbidity and mortality (4). Given the risks associated with delayed or unsuccessful extubation, determining readiness for extubation and predicting postextubation distress is a critical challenge in the ICU. Most of proposed predictors of postextubation distress either require special equipment, or are too complex for bedside use, or have a limited predictive value (3). To date, there are no simple clinical indices known to be powerful predictors of postextubation distress. Many mechanisms may impact on the ability to wean from mechanical ventilation, including spontaneous breathing-induced cardiac failure, and neuromuscular disorders, or alteration of lung resistance and compliance.

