#### **1.5 Goals and potential interests of our project:**

Our clinical study is designed to evaluate lung ultrasound, echocardiography and plasma BNP levels during the weaning period, in order to assess the relationship between these parameters and SBT or extubation failure. Thus, expected loss of lung aeration during clinical failure could be attributed to cardiac causes. These results could lead to assess prospectively SBT and extubation failures in ICU patients.

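### LUS predictive values are to come from ROC curves in one small cohort with no pre-set threshold; if the cut-off is taken from the same curve, its performance will on average look moderately too good

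*Protocol*

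**What the plan says.** The only statement on predictive performance is one sentence in section 6.2: "Predictive values of LUS will be determined by ROC (Receiving operating characteristics) curves". It does not say which LUS measure enters the curve, how a positive test is defined, or how performance is to be checked.

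Section 3.2.1 gives the regional points (0 to 3) and measurements before SBT, after SBT and after extubation, together with the overall variation. It gives no threshold.

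Section 6.1 sets the sample size from recruitment forecasts, because the study is a pilot without an expected difference. Its assumptions are that "SBT failure is found in about 15% of eligible patients in published series" and that extubation failure affects "approximately 35% of patients who passed the test of weaning". The intention is to "compare 55 patients without extubation failure with 30 patients failing extubation at 48 hours".

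On later use, section 1.5 says: "These results could lead to assess prospectively SBT and extubation failures in ICU patients".

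**The concern.** A predictive value needs a rule that divides patients into test-positive and test-negative. With no rule fixed beforehand and only one cohort, the rule would ordinarily be read off the ROC curve and then scored on the patients who produced the curve. A cut-off chosen because it does best in a sample does, on average, less well in new patients. With about 30 events the difference is not negligible.

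What is at stake is the description of LUS as a predictor. Sections 1.2 and 1.4 present prediction of failure as a hypothesis and an expected benefit, and section 1.5 foresees prospective assessment. An uncorrected cut-off and its apparent sensitivity could be taken forward as if they were established.

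**Working it through.** **The plan's own counts.** Inputs from section 6.1: 100 patients, 15% SBT failure, 35% extubation failure after a passed SBT.

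- Passing SBT: 100 × (1 − 0.15) = 85
- Failing extubation: 85 × 0.35 = 29.75, about 30
- Not failing: 85 − 29.75 = 55.25, about 55

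The stated 85 / 30 / 55 reproduces.

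**Optimism from choosing the cut-off in the same sample.** The protocol gives no distribution, AUC or selection rule, so these are assumptions: a normally distributed marker with equal variance in both groups, mean difference d = √2 × Φ⁻¹(AUC), and the cut-off that maximises Youden's index J = sensitivity + specificity − 1. In each of 4,000 simulated cohorts of 30 failures and 55 successes, the apparent performance at the chosen cut-off was compared with the true performance of that same cut-off, 1 − Φ(c − d) for sensitivity and Φ(c) for specificity. PPV and NPV use the cohort's failure proportion, 30/85. Means (apparent → true):

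| True AUC | Sensitivity | Specificity | PPV | NPV | J |
|---|---|---|---|---|---|
| 0.7 | 0.698 → 0.622 | 0.677 → 0.645 | 0.564 → 0.505 | 0.816 → 0.767 | 0.376 → 0.267 |
| 0.8 | 0.765 → 0.696 | 0.754 → 0.728 | 0.649 → 0.600 | 0.862 → 0.822 | 0.519 → 0.424 |
| 0.9 | 0.851 → 0.792 | 0.842 → 0.822 | 0.759 → 0.721 | 0.915 → 0.883 | 0.693 → 0.614 |

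Subtracting, the optimism is 6 to 8 points for sensitivity, 2 to 3 for specificity, 4 to 6 for PPV, 3 to 5 for NPV, and 0.08 to 0.11 for J. For a marker with no value (AUC 0.5), apparent J still averages 0.13 against a true 0.

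**Sensitivity to the assumptions.**

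- Coarse integer score (SD assumed to be 4 points, 2,000 runs): sensitivity optimism falls to 0.683 − 0.629 = 0.054 at AUC 0.7 and 0.841 − 0.802 = 0.039 at AUC 0.9, so about 4 to 5 points. Specificity stays at 2 to 3.
- Fewer failures: at an assumed 15% failure rate, 85 × 0.15 = 12.75, so 13 failures and 72 successes. Sensitivity optimism is then 0.739 − 0.604 = 0.135 at AUC 0.7 and 0.880 − 0.777 = 0.103 at AUC 0.9, so 10 to 14 points. The 15% lies inside the range in section 1, where "incidence of reintubation ranges between 3 and 30" per cent; reintubation is a narrower event than the protocol's extubation failure.

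**What is not biased.** The mean estimated AUC was 0.701, 0.799 and 0.900 for true values of 0.7, 0.8 and 0.9.

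**Random error for comparison.** The exact 95% CI for a sensitivity of 24/30 is 0.61 to 0.92. For an AUC of 0.80, the Hanley-McNeil formula has Q1 = 0.8/1.2 = 0.667 and Q2 = 2 × 0.64/1.8 = 0.711, so SE = √{[0.16 + 29 × (0.667 − 0.64) + 54 × (0.711 − 0.64)] / (30 × 55)} = 0.054, and the 95% CI is about 0.69 to 0.91.

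**Does the correction work?** With true AUC 0.75 and 30/55 patients, the mean apparent sum of sensitivity and specificity is 1.45 and the true sum 1.34. A bootstrap that repeats the cut-off selection in each resample brings the apparent figure to 1.38. It removes (1.45 − 1.38)/(1.45 − 1.34) = 0.64, about two thirds of the optimism.

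**The case against.** The strongest case against is that the defect is inferred. Section 6.2 does not mention a cut-off, a selection rule, sensitivity or specificity, and it does not rule out internal validation. A plan that reported only the AUC, fixed a threshold in advance, or bootstrapped the selection would also comply. Such details are commonly left to an SAP, which is not shown here. Deriving a cut-off in a self-declared pilot is legitimate, and the main objective (section 2.1) is a comparison of aeration changes between groups, not prediction. The sizes above rest on an assumed selection rule and distribution.

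Most of this stands, and it limits the point to a conditional one. It does not remove it. The protocol goes beyond silence: it commits to obtaining predictive values by ROC curves, in one cohort, with no threshold set. Read plainly, that leads to in-sample selection.

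Three stronger readings are tempting and are not supported:

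- A reader might infer that the protocol prescribes choosing and scoring the cut-off in the same patients, so that the results are certain to be inflated. The text does not say so, and the optimism is an average tendency, not a certainty for one data set.
- A reader might infer that the whole ROC analysis is biased. The AUC of one pre-named measure is not.
- A reader might infer that predictive values cannot be obtained this way because a ROC curve shows only sensitivity and specificity. In a prospective cohort they can be calculated at any threshold from the cohort's own failure rate. They then apply to that rate only: with sensitivity 0.70 and specificity 0.73, PPV = 0.70p / (0.70p + 0.27(1 − p)) is 0.58 at p = 0.35 but 0.31 at p = 0.15.

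**Conclusion.** The point holds in conditional form. If the cut-off comes from the same curve, apparent performance at 30 failures and 55 successes will on average be moderately optimistic, by the amounts in the table. This assumes a Youden cut-off, a binormal marker and a true AUC of 0.7 to 0.9. Sensitivity is affected most. The excess shrinks for a coarse score and grows if failures are fewer than planned. The bias is smaller than the sampling error, but confidence intervals around the apparent values do not correct it, because they are centred on the inflated figure. The primary group comparison is untouched. An amendment is worthwhile because the remedy uses only data already being collected.

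**What to change.** Replace the ROC sentence in section 6.2 with text that does the following:

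- Names in advance the LUS measure for the ROC analysis. It could be the before/after-SBT change already used for the primary comparison, or one stated time point. The choice is the sponsor's, with a reason given.
- Names the cut-off rule, for example maximum Youden's index.
- Makes the AUC with 95% CI the main measure of discrimination.
- Reports sensitivity, specificity, PPV and NPV at the derived cut-off with 95% CIs, after a bootstrap optimism correction that repeats the cut-off selection in each resample.
- States that PPV and NPV apply to the failure rate observed in this cohort.
- Labels the cut-off exploratory, pending external validation.

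The cost is a few lines of Stata code, with no extra patients or measurements. The reported figures will be slightly less favourable. About a third of the optimism may remain after the bootstrap, so the exploratory label is still needed.

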### 3 Description of the study

#### 3.1 Type of study

This is a biomedical research (RBM), prospective, open, non-randomized, two-center, study.

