##### 4.1 Procedure protocol

At inclusion, patient demographics, clinical, ventilatory and hemodynamic data are collected (see book collection in the appendix section).

Before SBT, we analyze arterial blood gases, plasma BNP levels, and we perform cardiac and lung echography.

At the end of SBT, we again analyze arterial blood gases, plasma BNP levels and cardiac/lung echography.

Blood sample is gathered from an indwelling arterial catheter, allowing both arterial blood gases analysis and measurements of BNP blood levels.

Echography is a noninvasive technique and is totally harmless to the patient. The use of ultrasound in intensive care is part of routine clinical practice, including weaning period, used to optimize patient management. Echography completion time is around 5 to 10 minutes per patient. The same doctor will perform all ultrasound evaluations at each center: [name] [name] in Clermont-Ferrand and [name] [name] at Pitié-Salpêtrière Hospital.

In case of SBT success, the patient is extubated and analysis of blood gases, BNP levels assessment and cardiac/lung echography are performed at H4-6.

Patients are followed until the 48th hour after extubation, and are considered as finally weaned in the absence of the need for oxygen therapy above 9L/min to maintain  $SpO_2 > 95\%$ , in the absence of the need for non-invasive or invasive reventilation (NIV or reintubation).

SBT failure criteria and reventilation criteria:

- $RR > 35/\text{min}$
- Chest indrawing
- $SpO_2 < 90\%$  under  $FiO_2$  of 50% or higher, or under  $O_2$  therapy flow  $> 9\text{L}/\text{min}$
- $HR > 120\text{ bpm}$  or change in  $HR > 20\%$
- $SBP > 200\text{ mmHg}$  or  $< 80\text{ mmHg}$
- Agitation
- Drowsiness

Extubation failure criteria: failure of extubation is an event defined at H48 post-extubation by:

- The need for NIV\*:
  - o the need for more than 3 hours of NIV per day after abdominal or thoracic surgery
  - o in a hypercapnic COPD patient
- $O_2\text{ mask} > 9\text{ l} / \text{min}$  for a  $SpO_2 > 92\%$ ;

- Clinical signs of respiratory distress: RR > 35/min, SpO2 < 90% under O2 > 9L/min, circulation, exhaustion, poor hemodynamic tolerance, HR > 120, SBP > 160 or < 90 mmHg, or poor tolerance with neurological agitation, impaired consciousness;
- The need for reintubation;
- Death within 48 hours after extubation.

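### Centre adjustment hangs on an intra-class correlation from only two centres, with no threshold or adjusted model, and neither named primary test can include centre

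*Protocol*

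**What the plan says.** Protocol section 3.1 describes a "prospective, open, non-randomized, two-center, study". Section 4.1 fixes the readers: "The same doctor will perform all ultrasound evaluations at each center".

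Section 6.2 compares the before/after SBT change in LUS between weaning failures and successes "by Student's t test if variables are normally distributed". Normality is checked with a Kolmogorov-Smirnov test, and "in the case of non-normal distribution, Mann-Whitney (or Wilcoxon) test will be applied". Predictive values of LUS are to come from ROC curves; the text does not say whether these use the absolute score or the change.

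On centre, the same section says: "The center-effect will be measured by the coefficient of intra-class correlation and taken into account in the different statistical analyses when necessary". It gives no ICC threshold and no model or stratified test to use if adjustment is judged necessary. Each test uses a 0.05 level: "we will reject the null hypothesis (hypothesis of no difference) for p-values below 0.05".

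Section 6.1 calls the study a pilot and gives the planned numbers: "Therefore a total of 100 patients will enable us to study 85 patients passing SBT", split into 55 without and 30 with extubation failure.

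**The concern.** The protocol commits to a specific statistic as the guide to whether centre matters, and that statistic carries very little information with two centres. If it did point to adjustment, the section names no primary analysis to switch to, because a two-sample t test and a Mann-Whitney test have no place for a centre term.

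Centre deserves care here because it is also the ultrasound reader. A constant difference between readers cancels in the before/after change. A reader or centre effect on the change itself does not. If such an effect exists and the centres also have different failure rates, a comparison that leaves centre out attributes part of it to weaning outcome.

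The choice of test is a second data-driven step. A Kolmogorov-Smirnov test against a normal with estimated mean and SD has little power at the size of the failure group. Student's test also assumes equal variances in groups planned at 30 and 55.

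**Working it through.** **Inputs from the protocol.** Two centres (3.1); one reader per centre (4.1); 100 patients, 15% SBT failure, 35% extubation failure among those who pass (6.1); level 0.05 (6.2), taken as two-sided because sidedness is not stated.

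**Planned numbers.** 100 × 0.85 = 85; 85 × 0.35 = 29.75, about 30; 85 - 29.75 = 55.25, about 55. These reproduce section 6.1.

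**Assumptions, not in the documents.** Centre split 43/42 unless stated; failure rates by centre; centre shift in LUS change, in SD units; ICC thresholds; error distributions; SD ratio between groups.

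**1. What an ICC from two centres can say.** For about m = 42.5 patients per centre, ICC = (F - 1)/(F + m - 1). The 95% limits come from F divided by the 97.5% point of F(1, 83), which is 5.21, and F multiplied by the 97.5% point of F(83, 1), which is 1,012.

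| F | ICC | 95% interval |
|---|---|---|
| 1 | 0.00 | -0.02 to 0.96 |
| 4 | 3/45.5 = 0.07 | -0.01 to 0.99 |
| 8 | 7/49.5 = 0.14 | 0.01 to 0.995 |

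With a true ICC of 0.10 and 42 patients per centre, 95% of simulated estimates fall between -0.02 and 0.40, and 33% are zero or below.

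**2. What an ICC threshold amounts to.** With equal centres, F = (m/2)d² = 21.25d², where d is the observed centre difference in SD units. Solving for F gives F = (1 + 41.5 × ICC)/(1 - ICC).
- ICC 0: F = 1, d = √(1/21.25) = 0.22.
- ICC 0.05: F = 3.075/0.95 = 3.24, d = 0.39.
- ICC 0.10: F = 5.15/0.90 = 5.72, d = 0.52.

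The ICC therefore re-expresses the observed centre difference. It takes no account of whether failure rates differ by centre.

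**3. Bias if centre is left out.** Take failure rates of 25% and 45%. Failures are 43 × 0.25 = 10.75 and 42 × 0.45 = 18.9; successes are 32.25 and 23.1. The second centre supplies 18.9/29.65 = 0.637 of failures and 23.1/55.35 = 0.417 of successes, a gap of 0.220. A 0.75 SD shift gives a spurious difference of 0.220 × 0.75 = 0.165 SD, and a 0.5 SD shift gives 0.110 SD. The standard error is about √(1/30 + 1/55) = 0.227 SD, so these are 0.73 and 0.48 standard errors. With equal failure rates the gap is zero and so is the bias.

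**4. Simulated type I error, no true group difference.**

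| Handling of centre | Setting | Type I error |
|---|---|---|
| Left out | 25% vs 45%, shift 0.5-0.75 SD | 8-11% |
| Left out | 20% vs 50%, shift 1 SD | about 26% |
| Left out | equal failure rates, normal errors | 5% or below |
| Adjusted if ICC > 0.05 or > 0.10 | settings with different failure rates, normal errors | about 5-6.5% |
| Adjusted if ICC > 0.05 or > 0.10 | skewed (exponential) errors | up to 7.5% |
| Always a fixed term | splits 43/42 and 60/25, normal and skewed errors | 4.4-5.7% |

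**5. Test selection.** Kolmogorov-Smirnov with estimated mean and SD detects exponential data in about 11% of samples at n = 30, 46% at n = 55 and 83% at n = 85. If the failure-group SD is 1.5-2 times that of the success group, Student's t has type I error of 8-10% at 30/55 and 11-16% at 20/65, while Welch's test stays near 5%. With equal variances and no centre shift, the gated procedure has type I error of 4.6-5.2% for normal and 5.1-6.0% for skewed data, so the gate alone adds at most about one point.

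**The case against.** The protocol does not ignore centre; it undertakes to allow for it where needed. A reader might infer that confounding will go uncorrected and that the error rate exceeds 5%. The documents do not support either. The larger figures above describe an analysis in which centre is never adjusted. In the scenarios that produce them, an ICC trigger at 0.05 or 0.10 nearly always fires: in 87-95% of runs at 0.75 SD and in 99-100% at 1 SD. The error then returns to about 5%. When the ICC is zero or negative, the observed centre difference is small (about 0.22 SD or less, step 2), which is where omission does least harm. This stands, and it limits the size of the point. It does not supply the missing threshold or model.

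The documents give no failure rates by centre, reader bias or SDs. Excess error therefore cannot be stated as fact, and a more variable failure group is only an assumption.

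A reader might say the normality test almost never rejects. That fits n = 30 but not n = 55 or 85, and section 6.2 does not say whether it is applied by group or pooled. Nor does the text say that the centre step follows the choice of test.

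A reader might also infer that SBT technique differs between centres, since the Summary describes pressure support and section 1.1 a T-tube. Nothing links either technique to a centre.

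Finally, a threshold and an adjusted model could be left to a statistical analysis plan. But the protocol goes further: it fixes the ICC as the measure and names primary tests that cannot hold a centre term.

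**Conclusion.** The concern holds as a weakness of method. An ICC with one between-centre degree of freedom is a poor basis for deciding whether to adjust, the decision rule and adjusted model are absent, and neither named primary test can include centre. Because centre and reader are fully aliased, an effect of either on LUS change, together with different failure rates by centre, would bias the comparison if centre were left out.

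On assumed values, the loss is a type I error of 8-11% in moderately unfavourable settings with centre omitted. It mostly disappears if a sensible trigger is used, and is absent when failure rates are equal. The Student's t inflation rests entirely on the assumed SD ratio. As this is a declared pilot with no powered hypothesis, the point ranks as a cheap improvement.

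**What to change.** In section 6.2, drop the ICC trigger and the normality pre-test. Make the primary analysis a linear model of LUS change on outcome group, with centre as an unconditional fixed effect and heteroscedasticity-robust (Welch-type) standard errors. Name a centre-stratified Wilcoxon (van Elteren) test as the sensitivity analysis. State whether the ROC analysis uses absolute LUS or its change; if absolute, stratify or adjust it by centre, because a constant reader offset does not cancel there.

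The cost is a change of wording and one degree of freedom: with 85 patients, 85 - 3 = 82 residual degrees of freedom instead of 85 - 2 = 83. No extra data or patients are needed. The fixed term does not separate reader from centre, which the design does not allow; it removes their joint average effect on LUS change from the group comparison.
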